#### Exclusion criteria

Known heart failure (grades I–IV of the New York Heart Association classification)History of effective bariatric surgery in the 10 years prior to selection.Patients with a history of clinically significant cardiovascular events in the 6 months prior to selection such as an acute cardiovascular event, stroke, transient ischemic attack, or coronary heart disease (angina, myocardial infarction, revascularization procedures).A weight loss of more than 5% in the 6 months prior to randomization.Current or history of significant alcohol consumption (< 5 years). For men, significant consumption is usually defined as more than 30 g of alcohol per day. For women, defined as more than 20 g of alcohol per day.Liver cirrhosis.Non-cirrhotic portal hypertension.Presence of esophageal and/or gastric varices.Hepatocarcinoma.Portal thrombosis.Pregnancy.Any other medical condition that may diminish life expectancy to <2 years, including known cancers.Indications of any other untreated, unstable or clinically significant immunological, endocrine, hematological, gastrointestinal, neurological, neoplastic, or psychiatric disease.Mental instability or incompetence such that the validity of the informed consent or the ability to comply with the study is uncertain.Positive antibodies to human immunodeficiency virus.Decompensated liver disease measured as follows:
Aspartate aminotransferase (AST) and/or ALT > 10 x upper limit of normality (LSN)Total bilirubin > 25 μmol/l (1.5 mg/dl).International normalized ratio > 1.4.Platelet count < 100 000/mm^3^.Serum creatinine levels > 135 μmol/l (> 1.53 mg/dl) in men and > 110 μmol/l (> 1.24 mg/dl) in women.Significant renal disease, including nephrotic syndrome, chronic renal disease (patients with markers of liver injury or estimated glomerular filtration rate [eGFR] of less than 60 ml/min/1.73 m^2^). If an abnormal value is obtained at the first screening visit, eGFR measurement may be repeated before randomization within the following time frame: minimum 4 weeks after the initial test and maximum 2 weeks before the intended randomization. Repeated abnormal eGFR (less than 60 ml/min/1,73 m^2^) leads to exclusion from the study.

### Who will take informed consent? {26a}

The informed consent of the TESLA-NASH study will be signed by all the subjects before their inclusion in the study. Additionally, by daily clinical practice, patients randomized in the experimental group will sign the endoscopic gastroplasty-specific informed consent form and patients in the control group will sign the laparoscopic vertical gastrectomy informed consent form.

### Additional consent provisions for collection and use of participant data and biological specimens {26b}

No collection samples

### Interventions

#### Explanation for the choice of comparators {6b}

Patients with obesity with or without metabolic syndrome, according to NCEP ATP-III (National Cholesterol Education Program’s Adult Treatment Panel III Report), and NASH diagnosed by liver biopsy will be included in the study.

After 10 weeks of the screening period, the patient will be randomized in experimental o control intervention.

#### Intervention description

The interventions and comparators description is shown in Table 1.

**Table 1 Tab1:** Interventions and comparators description

Groups	Interventions
**Experimental group**	The endoscopic technique is defined as a gastric restriction by means of continuous sutures of the entire gastric wall of the antrum and body, transmurally, in order to simulate a gastric sleeve, in the same way as the sleeve gastrectomy surgery. Gastroplasty is performed using an endoscopic suture system (Overstitch, Apollo endosurgery Inc., Austin, Texas, USA) inserted into a dual-channel endoscope (GIF-2T160.Olympus Medical System Corp., Tokyo, Japan)
**Control group**	The minimally invasive surgical technique is defined as a gastric restriction by means of excision of approximately 80% of the stomach along the greater curvature.

The surgery, LSG, will be performed by the study surgeons while the ESG will be carried out by the endoscopists

#### Criteria for discontinuing or modifying allocated interventions {11b}

In accordance with the revision of the Declaration of Helsinki and current regulations, the patient has the right to withdraw from the study at any time and for any reason, without prejudice to future medical care by his doctor and/or a referral site.

Patients who have withdrawn from the study cannot be included again in the study.

A patient may leave the study for any of the following reasons:
Withdrawal of the informed consent and/or refusal of treatment and/or lack of cooperation.Death of the patient.Decision of the principal investigator and/or sub-investigator in charge, if it is in the patient’s interest to stop the study.

#### Strategies to improve adherence to interventions {11c}

To verify the effectiveness of each technique and ensure patient’s safety, follow-up visits will occur after the interventions. Seven follow-up visits will be carried out over 24 months where the variables described in the protocol will be assessed by means of biochemical cholesterol, biomarkers of inflammation and lipid tests changes, cardiovascular events, quality of life and physical activity questionnaires progress, liver biopsy, abdominal ultrasound and non-invasive assessments of fibrosis, post-intervention dietary and lifestyle recommendations and revisions, records of the concomitant medication during the follow-up, and an evaluation of the safety by controlling adverse events and adverse reactions.

#### Relevant concomitant care permitted or prohibited during the trial {11d}

Any concomitant medication is allowed within daily clinical practice. The concomitant medication administered will be registered in the clinical report form (CRF) of the clinical trial.

#### Provisions for post-trial care {30}

This is a non-commercial study carried out by Spanish researchers whom are employees of the national public health system. The sponsor of the study is a non-profit organization, IDIVAL health research institute.

There is no compensation for the subjects participating in the clinical trial.

### Outcomes {12}

#### Primary outcome

Assessment of the efficacy of endoscopic vertical gastroplasty + lifestyle modification against laparoscopic vertical gastrectomy + lifestyle modification in the histological improvement of NASH from baseline to week 96 by the following:
Improvement of fibrosis in at least 1 stage without worsening of NASH.Resolution of NASH without worsening of fibrosis.

The resolution of NASH is defined as the histopathological disappearance of ballooning and the disappearance or persistence of minimal lobular inflammation (grade 0 or 1) using the NASH CRN scoring system with a type of general lesion that does not qualify as steatohepatitis. Worsening of fibrosis is defined as the progression of at least one stage.

For all the patients, a basal liver biopsy should be obtained prior to the execution of the therapeutic technique and a subsequent biopsy 96 weeks after the procedure should also be obtained.

To avoid inter-observer variability, the histological evaluation will be assessed by two local pathologists independently.

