#### Objective

The objective is to evaluate the efficacy of ESG + lifestyle modification versus LSG + lifestyle modification in resolving NASH without worsening of fibrosis.

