##### Sample size {14}

Previous studies have shown a resolution of NASH in the 85% of patients undergoing a bariatric surgery (69.6% in gastric tubing surgery) and a resolution of 25% in patients with a lifestyle intervention. A bilateral ratio comparison test was used for sample size calculation with a confidence level of 99%, a statistical power of 90%, and an assumption of 7% loss. Obtained sample to observe differences is *n*=30 (15 per treatment arm).

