### Statistical methods

#### Statistical methods for primary and secondary outcomes {20a}

Data will be analyzed using SPSS version 19. A descriptive baseline and end-of-follow-up analysis (week 96) of the data will be performed using the mean and standard deviation or the median and range where appropriate for quantitative data and percentage for qualitative data. Quantitative variables will be compared with Student’s *t* test and qualitative variables will be compared with *X*^2^. When variables do not follow a normal distribution, non-parametric tests should be used. Paired data tests will be used to analyze baseline and 96-week results.

All changes in efficacy parameters endpoints will be analyzed in an intention-to-treat and per-protocol analysis and grouped by randomized treatment.

The Intent-to-Treat (ITT) population will include all subjects randomized to treatment. The per-protocol (PP) population will be a subset of the ITT population, excluding subjects that violate key protocol criteria, with the exact list of exclusion reasons to be included in the statistical analysis plan (SAP).

The primary efficacy endpoint, by histopathological improvement of fibrosis by at least 1 stage without any worsening of NASH, and histopathological resolution of NASH without any worsening of the stage of fibrosis will be conducted on the intention-to-treat (ITT) population; so all randomized subjects will be included in the primary analysis.

Secondary endpoints analyzed by descriptive statistics and inferential statistics will include ANOVA. Non-parametric tests may be utilized such as Wilcoxon rank-sum.

For all tests, we will use 2-sided *p* values with alpha < 0.05 level of significance.

All safety variables (i.e., adverse events, laboratory data, vital signs, and ECG) will be summarized by treatment for all patients of the safety set. Descriptive statistics using appropriate summary statistics will be calculated for quantitative safety data as well as for the difference to baseline, when appropriate. In addition, a shift table describing out-of-normal range shifts will be provided for clinical laboratory results.

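### The protocol names one primary endpoint in its objective, design and sample size, but two in its outcome and statistics sections, with no rule for what counts as success

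*Protocol article*

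**What the plan says.** The protocol article describes the primary endpoint in five places.

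- **Objective {7}:** efficacy is judged "in resolving NASH without worsening of fibrosis". No other target is named.
- **Trial design {8}:** the same single target.
- **Sample size {14}:** the planning rates concern NASH resolution only. The section begins "Previous studies have shown a resolution of NASH in the 85% of patients" and adds 69.6% for gastric tubing surgery and 25% for lifestyle intervention. No rate for fibrosis improvement enters.
- **Outcomes {12}, Primary outcome:** two list items, which run together in the extracted text: "Improvement of fibrosis in at least 1 stage without worsening of NASH.Resolution of NASH without worsening of fibrosis". No conjunction, order or success rule links them.
- **Statistical methods {20a}:** both items again, under a singular noun and joined by a conjunction: "The primary efficacy endpoint, by histopathological improvement of fibrosis by at least 1 stage without any worsening of NASH, and histopathological resolution of NASH". All tests use two-sided p "values with alpha < 0.05 level of significance". No order and no split of alpha is given. The only item that this section hands to the SAP is the list of reasons for exclusion from the per-protocol population.

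**The concern.** Three sections describe a trial with one primary endpoint and two describe a trial with two. The two-endpoint text permits three readings: success on either endpoint, success on both, or one composite per patient. These have different false-positive rates and different power, and only the single-endpoint version was sized.

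The endpoints are not interchangeable. The inclusion criteria set only an upper limit on fibrosis and make explicit provision for stage 1 or below. A patient at stage 0 can meet the resolution endpoint but cannot improve by a stage. The trial is also open-label, so a success rule left open at the start could be settled after results by arm are known.

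**Working it through.** **Inputs**
- From Sample size {14}: resolution 85% vs 25%; 69.6% for gastric tubing surgery; "A bilateral ratio comparison test was used for sample size calculation", "with a confidence level of 99" per cent, "a statistical power of 90" per cent; 7% loss; 15 per arm.
- From Statistical methods {20a}: chi-square for qualitative variables, two-sided 0.05.
- Assumed: a common fibrosis rate of 65.5%. The Introduction gives this as the meta-analysis figure for any fibrosis improvement after bariatric surgery, so it is not the rate of the endpoint as defined here.
- Assumed: latent correlation between the two endpoints from 0 to 0.9. The protocol gives none.

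**Step 1: reproduce the sample size, to see which endpoint it serves.** With the unpooled formula,

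n = (z₀.₉₉₅ + z₀.₉₀)² × [p₁(1−p₁) + p₂(1−p₂)] / (p₁−p₂)²

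= (2.576 + 1.282)² × (0.1275 + 0.1875) / 0.60² = 13.02, so 14 per arm.

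Loss added as 14 × 1.07 = 14.98 gives 15 per arm, 30 in total, as stated. (Dividing by 0.93 gives 15.05, hence 16 per arm.) The figure is recovered from the resolution rates alone, so the fibrosis endpoint played no part in sizing.

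**Step 2: either endpoint suffices.** For two independent tests at a nominal 0.05, the error is 1 − 0.95² = 0.0975. For correlated normal test statistics it is 0.0951 at correlation 0.3, 0.0907 at 0.5, 0.0835 at 0.7 and 0.0704 at 0.9.

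At 15 per arm the uncorrected chi-square test has actual size 0.0547 at 69.6% and 0.0525 at 65.5%. Independence then gives 1 − (0.9453 × 0.9475) = 0.104. Simulation with correlated binary endpoints and no true difference gives:

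| Latent correlation | Either significant (uncorrected chi-square) |
|---|---|
| 0 | 0.104 |
| 0.3 | 0.103 |
| 0.5 | 0.099 |
| 0.7 | 0.098 |
| 0.9 | 0.089 |

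With Fisher's exact test or the Yates correction, the same settings give about 0.027 to 0.033, against about 0.015 to 0.017 for one test.

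**Step 3: both endpoints required.** The error cannot exceed that of one test. With no difference on either endpoint, simulation gives about 0.003 (correlation 0) to 0.018 (correlation 0.9). The cost is power. For resolution alone at 85% vs 25%, 15 per arm and 0.05, power is 0.945 by simulation (0.954 by the pooled normal approximation). With an assumed 65.5% vs 25% for fibrosis, that endpoint alone has power of about 0.614. Under independence the joint power is 0.945 × 0.614 = 0.58; simulation gives 0.58 to 0.61 across correlations 0 to 0.9. With an assumed 50% vs 25% for fibrosis, joint power is about 0.28 to 0.29.

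**Step 4: composite.** This is a single test, so the error is not inflated. It is a third endpoint, for which the protocol has no planning rate.

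**The case against.** A reader might infer that the protocol simply doubles its false-positive rate. The text does not support that. The statistics section uses a singular noun and joins the two parts with a conjunction, which allows a both-required or a composite reading, and neither inflates the error. Doubling is the consequence of one reading only.

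Three limits on the size also stand. The absolute figure depends on the test: with Fisher or Yates the error roughly doubles but stays under 0.05. The error is two-sided, so roughly half of the false positives would favour surgery, whereas the hypothesis concerns the endoscopic procedure doing at least as well. And 65.5% is a borrowed rate.

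Two textual points are fair. The abstract states a broader aim, improvement in liver histology, which fits a two-part outcome. The sample size section speaks of NASH resolution without the fibrosis condition, so its match to the objective is close but not exact.

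It can also be said that multiplicity rules belong in the SAP. That would answer a missing detail. It does not answer a protocol whose objective, design and sample size point to one endpoint while its outcome and statistics sections give two.

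**Conclusion.** The contradiction on the primary endpoint is real and lies within the protocol. Its consequence is conditional:

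- **Either suffices:** two-sided family-wise error of about 0.09 to 0.10 with the uncorrected chi-square test, against about 0.054 for one endpoint.
- **Both required:** no inflation, but power below that of the endpoint used for sizing, for example from about 0.95 to about 0.6 at 0.05.
- **Composite:** no inflation, and no planning basis.

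These figures rest on 15 analysed per arm, the assumed fibrosis rates, and latent correlations of 0 to 0.9. The power figures also take the protocol's own 85% vs 25% at face value. The sizing level of 0.01 differs from the testing level of 0.05, which is a separate matter; at 0.01 each, two independent tests would give 1 − 0.99² = 0.0199.

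This needs correcting because, as written, a positive trial is not defined.

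**What to change.** In the Primary outcome and Statistical methods sections, name resolution of NASH with no worsening of fibrosis at week 96 as the only primary endpoint. The objective and design already say this, and the sample size uses resolution rates. Make fibrosis improvement of at least one stage with no worsening of NASH the first key secondary endpoint, tested at 0.05 only if the primary is significant. This fixed order needs no alpha split and no extra patients.

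If the sponsor wishes to keep both as primary, the protocol must state the rule. Splitting alpha at 0.025 each holds the nominal error at or below 0.0494, and lowers power for resolution (85% vs 25%, 15 per arm, pooled approximation) from 0.954 to 0.908. Requiring both needs a planning rate for fibrosis and a new power calculation.

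The cost of the main proposal is that fibrosis loses primary status. The protocol sends all amendments to the ethics committee and the trial registry, and inclusion began in June 2020, so the change should be dated and justified without reference to outcome data by arm.

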#### Trial design {8}

The TESLA-NASH study is a randomized, controlled, open-label, unicentric clinical trial with a sanitary product, designed to evaluate the efficacy of two gastric techniques (endoscopic versus laparoscopic) in the resolution of NASH without worsening liver fibrosis.
Experimental group: ESG + lifestyle modificationsControl group: LSG + lifestyle modifications

A total of 30 eligible participants will be randomly assigned (stratified by the presence or absence of type II diabetes mellitus) to the experimental group or the control group with a 1:1 ratio. The participants will be recruited at the Hospital Marqués de Valdecilla from June 2020 to June 2021.

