#### Assignment of interventions: blinding

Given the nature of this study where surgical procedures are performed versus an endoscopic procedure, the study staff cannot be blinded.

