#### Who will be blinded {17a}

Not applicable

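### The reason given for not blinding anyone does not cover the two pathologists who grade the primary endpoint, so the week-96 biopsies may be read with knowledge of the arm

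*Protocol article*

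**What the plan says.** All references are to the protocol article.

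- **Trial design {8}:** "The TESLA-NASH study is a randomized, controlled, open-label, unicentric clinical trial with a sanitary product".
- **Primary outcome:** the endpoint is histological, from baseline to week 96, in two parts: "Improvement of fibrosis in at least 1 stage without worsening of NASH.Resolution of NASH without worsening of fibrosis". Resolution requires that ballooning has gone and lobular inflammation is at most grade 1, judged "using the NASH CRN scoring system with a type of general lesion that does not qualify as steatohepatitis". Worsening of fibrosis means progression by one stage or more.
- **Readers (same section):** "To avoid inter-observer variability, the histological evaluation will be assessed by two local pathologists independently".
- **Assignment of interventions: blinding:** the contrast between a surgical and an endoscopic technique is the only reason offered for the statement that "the study staff cannot be blinded".
- **Item {17a}, which asks for the blinded roles:** the whole answer is "Not applicable".

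No section says that the pathologists are masked to arm, biopsy order or clinical data.

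**The concern.** The stated obstacle to blinding is that the two procedures differ visibly. Operators, patients and follow-up staff cannot be kept from knowing which was done. The pathologist is in a different position: the specimen is liver, the interventions are on the stomach, and a slide can carry a code instead of a name. The article therefore gives a reason that fits some roles and then declares blinding irrelevant for everyone, including the two people whose grades decide the primary endpoint.

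Ballooning, lobular inflammation and the overall judgement of lesion type are matters of visual grading, and borderline cases occur. A reader at the same hospital who knows the arm can lean on those cases, in either direction and without intent. The Hypotheses section expects the endoscopic arm to do at least as well as surgery. A lean could therefore create a difference or hide one.

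A smaller issue sits in the same sentence. Two independent readings measure inter-observer variability; they do not remove it. Only a rule for combining them yields one value per patient.

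**Working it through.** **1. Does the reason cover the readers?**

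| Role | Can the procedure be hidden? | Covered by the stated reason? |
|---|---|---|
| Surgeons and endoscopists | No | Yes |
| Patients, follow-up staff | Not practically | Yes |
| Pathologists reading liver slides | Yes, by coding | No |

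The answer under {17a} is an explicit position, not a gap that a longer document would be expected to fill.

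**2. Which reading is exposed?** Under the Inclusion criteria, the diagnostic biopsy is taken within 6 months before randomization or during screening, and its result is needed for eligibility. That reading precedes allocation and cannot be influenced by it. The exposed readings are those at week 96 and any later re-reading of baseline slides.

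**3. Sample size used.** Sample size {14} gives 30 patients, 15 per arm. This reproduces from 85% versus 25%, two-sided alpha 0.01 and power 90% with the unpooled normal formula:

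n = (2.576 + 1.282)² × (0.85×0.15 + 0.25×0.75) / (0.60)² = 14.88 × 0.315 / 0.36 = 13.02, rounded up to 14; 14 × 1.07 = 14.98, so 15 per arm.

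The point here uses only the 15 per arm.

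**4. Effect of one reclassified patient.** 1/15 = 6.7 points on the risk difference; 2/15 = 13.3; 3/15 = 20.

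**5. Can one patient matter to the test?** The plan uses chi-square at two-sided 0.05 (Statistical methods {20a}). For illustrative counts, without continuity correction:

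- 11/15 versus 6/15: χ² = 30 × (11×9 − 4×6)² / (15×15×17×13) = 168,750 / 49,725 = 3.39, p = 0.065.
- 12/15 versus 6/15: χ² = 30 × (12×9 − 3×6)² / (15×15×18×12) = 243,000 / 48,600 = 5.00, p = 0.025.

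One patient's reading separates the two results.

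**6. Effect on the error rate, by assumption.** The article gives no figure for reader bias, so a range is assumed. Suppose both arms have a true resolution rate of 69.6% (the sleeve-surgery figure in Sample size {14}) and the lean shifts the observed difference by d, split evenly between arms. With the normal approximation:

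- SE under the null = √(2 × 0.696 × 0.304 / 15) = 0.168, so the critical difference is 1.96 × 0.168 = 0.329.
- d = 0.10 (rates 0.746 and 0.646): SE = 0.167; z = (0.10 − 0.329)/0.167 = −1.37; probability 8.5%.
- d = 0.20 (rates 0.796 and 0.596): SE = 0.164; z = (0.20 − 0.329)/0.164 = −0.79; probability 21.5%.

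The nominal chance in that direction is 2.5%. Shifts of 10 and 20 points correspond to 1.5 and 3 patients of 15.

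**The case against.** **The article never says that the pathologists will know the arm.** This is true. Concealment mechanism {16b} and Implementation {16c} route the allocation to the study coordinator and then the patient, and nobody is told to inform pathology. A reader might infer that the slides will be read unmasked and the result biased; the text does not support that. What stands is that no masking is provided, the readers are local to a single open-label centre, and the item that should provide masking is answered in the negative.

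**Baseline and visit.** A reader might extend the concern to the eligibility reading or treat knowledge of the visit as an equal threat. The eligibility reading precedes randomization. Both arms are biopsied at baseline and week 96, so knowing the visit would tend to shift both arms alike. It bears mainly on within-arm change, not on the comparison between arms. Compulsory re-reading of baseline slides is also debatable: it could reclassify a randomized patient as not meeting the histological entry criterion, while the primary analysis keeps all randomized subjects.

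**Discordant readings.** It is tempting to say that patients on whom the readers disagree have no defined outcome, or that the more favourable reading could be picked afterwards, and to put a number on them. The documents do not support this. A rule for combining two readings is detail that an article commonly leaves to the full protocol or analysis plan, neither of which is shown, and no agreement rate is given. Double reading is also a recognised safeguard, and the sentence may simply mean less reliance on one observer. Only the narrow remark survives: independence alone does not avoid variability.

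**The 6.7 points apply to any trial with 15 per arm.** Correct. The figure shows how little room for reading error this trial has; it is not evidence that error will occur.

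**Conclusion.** The point holds in limited form. The justification for not blinding does not reach the outcome readers, and the answer under {17a} forgoes a feasible safeguard on the primary endpoint. The exposure lies in the week-96 readings. One reclassified patient is worth 6.7 points, and in the illustrative counts one patient decides significance at 0.05. The false-positive figures of 8.5% and 21.5% in the favoured direction rest on an assumed shift of 10 to 20 points and equal true rates of 69.6%. They show sensitivity and are not a forecast. The remark on double reading is secondary and depends on what the full protocol or analysis plan already contains.

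**What to change.** 1. Under {17a}, replace the current answer with a statement that both pathologists are masked to treatment arm, and that they read coded week-96 slides, and any baseline slides that are re-read, without clinical data. In the blinding section, limit the stated reason to the roles it fits.
2. If the full protocol or analysis plan does not already say so, state that a masked consensus of the same two pathologists is the value that enters the endpoint.

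Cost: someone other than the two readers codes the slides and holds the key, and there is a consensus session if item 2 is adopted. No extra biopsy or pathologist is needed, and the sample size stays at 30.
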